#### Clients

The eligibility criteria for participation in the client surveys were being older than 18 years, being able to give informed consent to participation, being a responsive patient, and having sufficient skills in the German language. Clients (i.e. patients and individuals in elderly care in residencies and at home) are contacted in the participating healthcare organisations and receive a booklet with a brief description of the survey and data privacy information. All clients are required to consent explicitly to participate in the study before data collection. At baseline, T1 and T2 follow-up, approximately 600 patients and 150 individuals in elderly care will be surveyed successively in a cross-sectional design in the intervention and control wards. Participation in the client surveys is anonymous. The outcome data on clients are collected by interviewers either as self-administered questionnaires, or personal interviews upon clients’ request. The interviewers receive a three-hour training in survey methodology provided by the authors from Ulm University before data collection.

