### Randomisation and implementation

Healthcare workers registered for the surveys by filling out a registration form addressed to Ulm University including personal information and the name of the ward they usually work in. Wards were then aggregated by the authors at Ulm University in clusters as described above, and stratified by hospital and elderly care ward. A list containing hospitals, clusters and number of registered participants was provided by the first author to the Institute of Epidemiology and Medical Biometry at Ulm University which generated the random allocation sequence and assigned clusters to interventions for the hospitals, independently from the authors at Ulm University and the consultants providing the intervention. The randomisation of clusters in the hospitals was performed in two steps with the statistical environment R. In the first step, the probability of being assigned to the intervention group was proportional to cluster size in each hospital, and a total of 10 clusters (i.e., one intervention cluster per hospital) were allocated to the intervention arm. Given the large variation of cluster sizes (Fig. 2), a sampling schedule proportional to size was required in the first step in order to ensure the generalisability of results by including the largest clusters in the hospitals, and to counter the expected power loss due to cluster and individual sample attrition in the subsequent follow-up measurements. In the second step, the random allocation proceeded by simple random sampling. However, given that only four consultants provide the intervention, a 1:1 allocation scheme for the remaining clusters was not feasible due to personnel limitations. Thus, the number of additional clusters in the intervention group in the hospitals was limited to 10. On the other hand, since the elderly care centre comprises only four wards, a simple random allocation in proportion 1:1 was performed in that case by the first author at Ulm University.

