**Individuals in elderly care (*****n*** **= 150)**			
*Age*			0
Age 50–79	42.9	24.2	
Age 80–89	50.0	49.5	
Age 90 and older	7.1	26.3	
*Sex*			0
Male	42.9	28.4	
Female	57.1	71.6	
Years being in elderly care	4.54 (3.74)	3.96 (3.78)	8
*Psychometric scales*			
Trust	3.29 (0.72)	3.76 (0.43)	7
Support	3.07 (0.82)	3.60 (0.45)	9
Decisional control	4.10 (0.89)	4.47 (0.67)	12
Person-focused care	3.19 (1.04)	3.30 (1.20)	10

The estimates of the effective sample size (N_eff_) and the ICC corresponding to the workers’ physical and mental work ability were N_eff_ = 345 and 423, and ICC = 0.05 and 0.01, respectively. The average cluster size in the workers sample was m = 6.53, which yields design effect estimates of DE = 1.29 and 1.05 for the main outcomes. Thus, it will be possible to estimate effect sizes of at least 0.30 and 0.27 at the 80% power and 5% significance levels, for the workers’ physical and mental work ability, respectively. The estimates for the patients dataset were N_eff_ = 234, average ICC = 0.09, m = 19.5, and DE = 2.7. Since data of approximately 1200 additional patients will be collected cross-sectionally at the T1 and T2 follow-ups, a final effective sample size of approximately 234*3 = 702, and an average effect size of about 0.21 concerning patients satisfaction with care may be estimated at the 80% power and 5% significance levels. Finally, the power analysis for the elderly care dataset yielded an average ICC = 0.17, m = 30.7, and DE = 6.32, and an effective sample size of 24 per survey. Thus, for this dataset, at the end of the study, an effect size of about 0.66 can be estimated at the 80% power and 5% significance levels with a final effective sample size N_eff_ = 74 of elderly care clients.

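### The elderly-care columns of Table 2 cannot add up to the stated 150 clients, and the elderly-care power figures mix client totals; on one base the effective size is about 20 to 21 per survey, not 24

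*Protocol article*

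**What the plan says.** The Clients section plans that "approximately 600 patients and 150 individuals in elderly care will be surveyed successively in a cross-sectional design", with both intervention and control wards included. It adds: "Participation in the client surveys is anonymous".

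Under Randomisation and implementation, the article explains that "since the elderly care centre comprises only four wards, a simple random allocation in proportion 1:1 was performed". That means two wards per arm.

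The elderly-care block of Table 2 carries n = 150. It gives percentages by arm (control first, then intervention) but no arm sizes. The age rows are "Age 50–79 42.9 24.2", "Age 80–89 50.0 49.5" and "Age 90 and older 7.1 26.3". The sex rows are 42.9 and 28.4 (male), and 57.1 and 71.6 (female). The missing count is 0 for age and 0 for sex.

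The power paragraph after Table 2 gives, for elderly care, "average ICC = 0.17, m = 30.7, and DE = 6.32, and an effective sample size of 24 per survey". It then gives a final effective size of 74 and a detectable effect of about 0.66 at 80% power and 5% significance.

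**The concern.** If no age or sex value is missing, all 150 clients should appear in the two columns, and the percentages should be reproducible from two whole-number arm sizes that sum to 150. They are not.

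The power sentence has a related problem. Its cluster size and its effective sample size cannot both come from the same number of clients in four wards, and its design effect does not follow from the ICC and cluster size printed beside it.

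At stake is how much information the elderly-care comparison carries. The table does not show how many control clients stand behind the largest baseline gaps among the satisfaction scales in Table 2 (trust 3.29 against 3.76, support 3.07 against 3.60). The stated detectable effect is also more favourable than the article's own inputs allow.

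**Working it through.** **1. The plan's own figures.**
- Effective size per survey: 150 / 6.32 = 23.7, which rounds to the stated 24. This works only with 150 clients.
- Detectable effect, two-sided 5% and 80% power with equal arms (two-sidedness is assumed): (1.960 + 0.842) × √(4/74) = 0.65, or 0.66 with the t distribution. The stated 0.66 is reproduced.
- Design effect: 1 + 0.17 × (30.7 − 1) = 6.05, not 6.32. Rounding of the ICC does not close the gap: 0.165 to 0.175 gives 5.90 to 6.20, and 6.32 needs an ICC of 0.179.
- Final effective size: 3 × 24 = 72, whereas 450 / 6.05 = 74.4. The 24 therefore fits a design effect of 6.32, and the 74 fits one of 6.05.

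**2. Arm sizes in Table 2.** Every arm size from 1 to 150 was searched for whole-number counts that sum to the arm size and round to all printed age and sex percentages.
- Intervention: only 95 fits (age 23/47/25; sex 27/68).
- Control: only multiples of 14 fit (for example 28: age 12/14/2; sex 12/16).
- A total of 150 would need 150 − 95 = 55 controls, which is not a multiple of 14.
- With the tolerance widened to 0.2 percentage points, still no pair of arm sizes sums to 150.
- Totals that fit are 95 + 14 = 109, 95 + 28 = 123 and 95 + 42 = 137. The next is 95 + 56 = 151, one above the printed n.

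As a check on the method, the age rows of the other two blocks do reach their totals: patients 445 + 183 = 628 = 632 − 4, and workers 238 + 147 = 385 = 386 − 1. The mismatch is confined to elderly care.

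**3. Cluster size.** 30.7 × 4 wards = 122.8, so about 123 clients. With 150 clients the mean would be 150 / 4 = 37.5.

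**4. One consistent base.** For N clients in four wards at the stated ICC of 0.17: m = N/4, DE = 1 + 0.17 × (m − 1), effective size = N/DE. The three-survey total assumes that the baseline numbers repeat. The detectable effect is for equal arms, by the normal formula.

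| Clients | m | DE | Effective size per survey | Over three surveys | Detectable effect |
|---|---|---|---|---|---|
| 109 | 27.25 | 5.46 | 20.0 | 59.9 | 0.72 |
| 123 | 30.75 | 6.06 | 20.3 | 60.9 | 0.72 |
| 137 | 34.25 | 6.65 | 20.6 | 61.8 | 0.71 |
| 150 | 37.50 | 7.21 | 20.8 | 62.5 | 0.71 |
| 151 | 37.75 | 7.25 | 20.8 | 62.5 | 0.71 |

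The t-based version, which gives 0.66 at an effective size of 74, gives 0.73 for 123 clients and 0.72 for 150.

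**5. Unequal arms.** Replace 4/N_eff by 1/(N_eff·f) + 1/(N_eff·(1 − f)), where f is the intervention share. With 95:28, f = 0.772 and N_eff = 60.9, so the detectable effect is about 0.86. With 95:56, f = 0.629 and N_eff = 62.5, so it is about 0.73.

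**The case against.** The strongest reply is that only the mismatch is proven and its cause is not. A reader might infer that about 27 anonymous clients (150 − 123) have no trial arm, that the table hides this by printing zero missing, and that the same loss will recur at T1 and T2. The document does not support this.

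- The control number is not fixed. Controls of 14, 28 or 42 all fit, and 56 fits if the true total is 151, in which case nobody is unaccounted for.
- The choice of 28 rests on reading m as a simple mean over four wards. Even then 123 / 4 = 30.75 prints as 30.7 only if truncated.
- The Table 2 caption defines the missing column per variable or scale. The zeros concern age and sex and say nothing about arm.
- Anonymity means that the person is not identified, not that the ward is unrecorded. Clients are approached within the participating organisations and interviewers collect the data. Nothing shows that ward labels were lost, so neither the recurrence nor a ward code on the forms as a remedy is justified at present.

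These objections stand, and the point does not depend on those inferences.

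It can also be said that the consequence is small. The Discussion states that the second hypothesis cannot be investigated in the elderly-care data because there are too few clusters, and Table 4 openly shows 96 complete cases. That limits the weight of the point but does not correct the printed figures: the power paragraph still presents 0.66 as attainable. The correction also does not rest on 123 clients, since every base in the table above gives about 20 to 21.

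**Conclusion.** The point holds as a reporting and arithmetic error. The elderly-care columns of Table 2 cannot describe 150 clients with complete age and sex. The cause is open: a wrong n, a count that is off by one, or clients left out of the columns.

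The power sentence takes its cluster size from about 123 clients and its effective size from 150, and its design effect is not the one its inputs give. On a consistent base the effective size is about 20 to 21 per survey rather than 24. For 123 or 150 clients that makes about 61 to 62 over three surveys rather than 74, with a detectable effect of about 0.71 to 0.72 with equal arms rather than 0.66. It would be larger, about 0.86, if the arms are as unequal as 95:28.

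This rests on the stated ICC of 0.17, four wards, a simple mean cluster size, and baseline numbers repeating at both follow-ups. It concerns a secondary outcome in one centre and does not touch the primary analysis.

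**What to change.** Print the arm denominators for the elderly-care block of Table 2, reconcile them with n = 150, and account for any clients who are in neither column. Then recompute the mean cluster size, design effect, effective size and detectable effect from one set of clients, namely those who can be assigned to a ward and an arm, using the actual split between arms. State how many clusters and records the mean cluster size is based on.

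A change to the client forms is warranted only if the reconciliation shows that ward labels were lost.

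The cost is a corrected table, a corrected paragraph and a slightly less favourable stated effect size. No new data are needed.

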**Patients (*****n*** **= 577)**								
**Dependent variables:**	**Trust in carers**		**Support by carers**		**Availability of carers**		**Decisional control over care**	
	**Beta (SE)**	**95% CI**	**Beta (SE)**	**95% CI**	**Beta (SE)**	**95% CI**	**Beta (SE)**	**95% CI**
Intercept	3.44 (0.65)	[2.16; 4.83]	3.35 (0.69)	[2.16; 4.82]	3.59 (0.64)	[2.42; 4.95]	4.54 (0.68)	[3.35; 5.94]
Intervention (ref. control)	0.03 (0.09)	[−0.16; 0.22]	0.06 (0.09)	[−0.11; 0.23]	0.04 (0.09)	[−0.16; 0.19]	− 0.01 (0.09)	[− 0.20; 0.16]
Physical work ability	0.00 (0.07)	[−0.14; 0.13]	0.01 (0.07)	[−0.13; 0.13]	0.01 (0.07)	[−0.15; 0.13]	0.02 (0.07)	[−0.13; 0.16]
Mental work ability	−0.00 (0.09)	[−0.17; 0.20]	0.01 (0.10)	[−0.17; 0.20]	− 0.05 (0.09)	[− 0.23; 0.13]	−0.07 (0.10)	[− 0.26; 0.10]
ERI	0.01 (0.25)	[−0.48; 0.47]	0.11 (0.25)	[−0.34; 0.64]	0.04 (0.26)	[−0.43; 0.56]	0.32 (0.26)	[−0.26; 0.79]
Overcommitment	−0.01 (0.18)	[−0.36; 0.35]	− 0.11 (0.19)	[− 0.43; 0.28]	−0.09 (0.18)	[− 0.43; 0.29]	−0.22 (0.19)	[− 0.57; 0.17]
DIC	902		1044		985		1067	
Residual variance	0.550		0.607		0.583		0.617	
**Individuals in elderly care (*****n*** **= 96)**								
**Dependent variables:**	**Trust in carers**		**Support by carers**		**Decisional control over care**		**Person-focused care**	
	**Beta (SE)**	**95% CI**	**Beta (SE)**	**95% CI**	**Beta (SE)**	**95% CI**	**Beta (SE)**	**95% CI**
Intercept	2.96 (0.56)	[1.76; 3.97]	3.09 (0.59)	[1.98; 4.30]	4.19 (0.57)	[3.13; 5.31]	3.69 (0.60)	[2.48; 4.83]
General health	0.13 (0.12)	[−0.13; 0.35]	0.08 (0.12)	[−0.15; 0.33]	−0.05 (0.12)	[−0.28; 0.19]	0.05 (0.13)	[−0.20; 0.29]
Intervention (ref. control)	0.38 (0.38)	[−0.31; 1.13]	0.39 (0.39)	[−0.39; 1.12]	0.22 (0.39)	[−0.50; 1.01]	0.16 (0.38)	[−0.57; 0.86]
DIC	212		207		221		292	
Residual variance	0.899		0.890		0.908		1.018	

## Discussion

The results at baseline suggest that the random allocation of clusters was satisfactory, since no substantial differences were observed between the intervention and control arm regarding the primary outcomes. According to the power analyses reported in the results section, one strength of the intervention is that effect sizes of at least 0.30 and 0.27 can be estimated at the 80% power and 5% significance levels, for physical and mental work ability of workers, respectively. Given that previous randomised organisational interventions have reported even larger effect sizes (standardised mean differences of − 1.23, − 0.55 and − 0.35) [7], the present study has sufficient power to detect substantial changes in the main outcomes.

A further strength of the study concerns the indication of an acceptable internal validity. Mainly successfully and widely tested questionnaires showing satisfying to good psychometric properties in previous studies [24, 31–35] and the present intervention as well (average Cronbach’s alpha over all instruments 0.74, see Supplementary material 1), were applied to measure independent (e.g., workload) and dependent variables (e.g., work ability, clients’ satisfaction). These measures allow comparisons of the present results with findings from other studies. Concerning the first study hypothesis, the results show associations of measures of effort-reward imbalance with work ability in workers. Hence, it is plausible to expect that a reduction of workload may result in increases of perceived work ability. In addition, the results indicate that these associations are mediated by perceived health (model 3 in Table 3). This mediation has been hypothesised previously, but has not been shown empirically so far [36]. However, the second hypothesis stating that the reduction of workload increases patients satisfaction did not receive support, since no cross-sectional associations were observed between workload and patients satisfaction (Table 4). Due to the low number of clusters in the elderly care centre, the second hypothesis cannot be investigated with the elderly care dataset.

Besides the consideration of the primary and secondary outcomes described in the methods section, by the end of the study further analyses may be performed in order to investigate how the intervention measures are related to specific working conditions. However, as far as the intervention measures are proposed by the workers themselves, the feasibility and scope of such additional statistical analyses will depend on the type and number of measures being actually implemented, the type of psychosocial factors potentially targeted by the interventions, and the extent to which specific intervention targets may be aggregated across clusters as individual, inter-personal and structural measures (see methods section). At the same time, the results obtained from the process evaluation will be used to inform the interpretation of results by focusing, among others, on the commitment of stakeholders, management and workers, and the potential role of collective self-efficacy expectations.

Because the overall participation rate in the intervention was rather low (13%), some basic socio-demographic statistics of the sample were compared to the corresponding values of the population of carers obtained from available hospital records. It was found that the participants are on average older than the whole population of hospital carers (46 vs. 43 years old), have a longer working experience (20 years vs. 14 years), and the proportion of males in the sample is slightly larger (17% vs. 22%). In view of these differences, the results of the present intervention should be interpreted with some caution regarding younger carers with less work experience.

Although the low participation rate at the individual level is an important limitation of the present study, several observations indicate that (1) participating workers are representative of the eligible healthcare workers, (2) the intervention measures are tailored to the workers’ needs and, (3) consequently, they may be effective at improving the working conditions in the wards. First, the number of wards included in the intervention account for about 68% of all hospital wards. Hence, even though the participation rate at the individual level is low (13%), the ward coverage is high (68%). Second, as stated in the methods section, the intervention is performed at the ward level, and, hence, the number of workers taking part in, and receiving, the intervention is actually higher than the number of workers filling out the questionnaires. Thus, the intervention measures are expected to address the most relevant issues for all workers in the intervention wards. Finally, the intervention measures are proposed and prioritised by the workers themselves during the interviews and workshops. Consequently, it is likely that these measures are effective at improving the working conditions in the intervention wards.

## Conclusions

In conclusion, the results suggest that the implementation of the study design has been satisfactory so far. The intervention is expected to provide evidence of relatively small to medium-size effects of the intervention activities on the work ability of healthcare workers and on clients’ satisfaction with care.

## Data Availability

Due to data protection regulations there is no permission to make the datasets available to third parties.

## Abbreviations

CI: Confidence interval
DE: Design effect
DIC: Deviance Information Criterion
ERI: Effort-reward imbalance
GLM: Generalised linear-mixed
ICC: Intraclass correlation coefficient
M: Average cluster size
N_eff_: Effective sample size
